#### Headache intensity and duration

2.11.4

Current as well as mean and maximum headache pain intensity (NRS 0–10) as well as headache duration (in hours) since LP (t3) or since the last survey (t4, t5) were assessed.

#### Use of on-demand pain medication

2.11.5

The use of on-demand pain medication (binary yes/no response) since LP (t3) or since last survey (t4, t5) was assessed.

#### Perceived warmth and competence of the physician

2.11.6

At t2, the perceived warmth and competence of the physician were assessed using 12 items rated on a 5-point scale (1 = not at all to 5 = extremely) (Seewald and Rief, 2023). The “warmth” subscale score was calculated as the mean of items 1–6, while the “competence” subscale score was calculated as the mean of items 7–12.

#### Satisfaction with the procedure

2.11.7

Patients were asked to rate their overall satisfaction with the procedure 3 h after LP (t3) based on the German school grading system from 1 to 6, where 1 is the best grade and 6 is the worst grade.

### Study schedule and data collection

2.12

Figure 1 displays an overview of the study schedule. The main investigation period spanned from inclusion to 72 h (i.e., 3 days) after LP. A follow-up survey was conducted 3 months after LP. After enrollment, participants were assigned a unique pseudonym using the software ALIIAS (Englert et al., 2023). ALIIAS is equipped with integration to LimeSurvey (LimeSurvey GmbH, Hamburg, Germany), an open-source web server-based survey system, which was used to collect all digital survey data in this study (Klieve et al., 2010). Each survey time point consisted of a digital survey, which the patient completed alone without any assistance, as well as a subsequent interview by the blinded study assistant, who recorded the answers in a separate online survey. Only at survey time point t2 (directly after the doctor’s explanation of the LP) did the patient exclusively complete an online survey without a subsequent interview. Table 2 summarizes the collected data and the questionnaires used.

**Figure 1 fig1:**
[figure not shown]
Study schedule at a glance. Inpatients in the neurology department of the University Hospital Essen requiring a diagnostic lumbar puncture (LP) were recruited to reach the target of N = 80. Screening and enrollment with obtaining consent were followed by the baseline survey (t1). Patients were randomized (n = 40 per group) to either the group receiving informed consent procedure (ICP) with the standard-of-care (SOC, blue), or optimized communication strategies (OPT, orange), some of which are displayed (orange arrows). A second survey follows after ICP (t2). The LP is performed, and surveys follow at 3 h (t3), 24 h (t4), and 72 h (t5) after LP. The completion of t5 marks the end of the main investigation period, in which the primary outcome—headache-related impairment on a numeric rating scale (NRS) from 0 to 10—is assessed. A follow-up online survey and telephone interview are performed 3 months after LP (t6). Created in BioRender. ([name], 2025).

**Table 2 tab2:** Overview of collected data and surveyed questionnaires.

Time point	Data entered directly by the patient (web-based survey)	Data provided by interview and entered by blinded study assistant
t1—Baseline assessments	Trait anxiety and depression (STADI-Trait) Baseline generic symptoms (modified GASE baseline) during past 7 days Current headache intensity	Demographic and biometric characteristics Medication BP and HR at admission Alcohol consumption Pack years Neurological symptoms Knowledge of (suspected) diagnosis Illness perception (modified B-IPQ) Previous experiences with similar procedures From physician: Reason for admission, LP indication, and (suspected) diagnosis
ICP (informed consent procedure)		Duration of physician contact during consent Copy of print ICP leaflet requested Transcript of audio recording
t2—after ICP	Treatment expectations (**modified TEX-Q**) State anxiety (**STAI-state**)	
LP (lumbar puncture)		Duration of physician contact during LP Anxiety before needle insertion 0-10 Needle insertion pain Amount of CSF collected in ml Needle bore size in gauge (G), needle length in mm Count of attempts
t3—3 h after LP	Current pain at needle insertion site Congruence with expectation Generic symptoms and LP side-effect attribution (modified GASE) **Current headache intensity** **Headache-related impairment since LP** **Duration of headache since LP (in hours)** **Minimum, maximum, and mean headache intensity since LP** Usage of the print ICP leaflet **Warmth and competence (W&C)** **Overall satisfaction with procedure**	Fluid intake in liters since LP Duration of bedrest in minutes If headache was present: Headache features (quality, localization, accompanying symptoms, restriction of physical activity) **Request for on-demand pain medication**
t4—24 h after LP	Generic symptoms and LP side-effect attribution (modified GASE) **Current headache intensity** **Headache-related impairment since t3** **Duration of headache since t3 (in hours)** **Minimum, maximum, and mean headache intensity since t3**	If headache was present: Headache features (quality, localization, accompanying symptoms, restriction of physical activity) **Request for on-demand pain medication**
t5—72 h after LP	Generic symptoms and LP side-effect attribution (modified GASE) **Current headache intensity** **Headache-related impairment since t4** **Duration of headache since t4 (in hours)** **Minimum, maximum, and mean headache intensity since t4** Belief about group allocation	If headache was present: Headache features (quality, localization, accompanying symptoms, restriction of physical activity) **Request for on-demand pain medication**
t6—3 months after LP	Generic symptoms (modified GASE) during past seven days Current headache intensity Headache-related impairment since LP Minimum, maximum, and mean headache intensity since LP Overall satisfaction with procedure Belief about group allocation Belief about study goal	Knowledge of (suspected) diagnosis after inpatient stay Illness perception (modified B-IPQ) Pre-existence of diagnosis of primary headache Average number of headache days and days with headache pain medication per month in the three months before and after LP Occurrence of new persistent headache since LP Headache features (quality, localization, duration of attacks, accompanying symptoms, restriction of physical activity) From physician and medical records: confirmation of diagnosis/suspicion

At all survey time points (t1–t6), a blinded study assistant collected patients’ data on the electronic study tablet. All data until t3 were collected in the hospital, while t4 and t5 were collected via an online survey and telephone interview if the patient had already been discharged. During the informed consent procedure (ICP) and lumbar puncture (LP), data were collected by the unblinded study physician. Assessments of the main (bold and underlined) and secondary outcomes (bold) are highlighted.

B-IPQ, Brief Illness Perception Questionnaire (Broadbent et al., 2006); GASE, General Assessment of Side Effects (Rief et al., 2011); ICP, Informed consent procedure; LP, Lumbar puncture; STADI-Trait, trait subscale of the State–Trait Anxiety and Depression Inventory (Laux et al., 2013); STAI-state, state subscale of the State–Trait Anxiety Inventory (Ferreira and Murray, 1983; Laux et al., 2013); TEX-Q, Treatment Expectation Questionnaire (Shedden-Mora et al., 2023); W&C, warmth and competence of the physician (Seewald and Rief, 2023); BP, blood pressure; HR, heart rate.

From inclusion to the survey time point 3 h after the lumbar puncture, the study took place exclusively during the inpatient stay in the clinic using the electronic study tablet and in direct personal conversation with the blinded study assistant. All other time points either occurred during the inpatient stay or after the patient’s discharge; in the latter case, the surveys were completed on the patient’s own electronic device and the interview was conducted by telephone.

The main and secondary outcomes were assessed at different time points, as described above. Since this study is part of a larger collaborative research effort investigating treatment expectations and potential modulators in different settings,^1^ participants were also asked to complete additional psychological questionnaires and provide biometric, demographic, and health data.

#### Survey time point 1 (t1)—baseline assessments

2.12.1

After enrollment, patients completed questionnaires to assess trait anxiety and depression [trait subscale of the State–Trait Anxiety and Depression Inventory, STADI-Trait (Laux et al., 2013)] and the baseline presence and severity of the following symptoms during the past 7 days: nausea, headache, vertigo, back pain, changes of vision, hearing or sensation, and photo- or phonophobia symptoms [modified General Assessment of Side Effects, GASE (Rief et al., 2011)]. Current headache intensity was assessed on a numerical rating scale (NRS) from 0 to 10. Basic demographic and biometric characteristics were recorded (age, sex, education, height and weight, blood pressure, and heart rate at admission) as well as current medication, days with alcohol consumption per month, and nicotine consumption (in pack years). The reason for admission was stated freely (e.g., neurological symptoms or recent findings requiring further investigation). The presence of a suspected or known underlying neurological diagnosis was also recorded. Illness perception was assessed using the following three items from the Brief Illness Perception Questionnaire (modified B-IPQ) (Broadbent et al., 2006): experience of symptoms, impact on daily life, and degree of concern. Information was further obtained on patients’ prior experiences with similar procedures, that is, epidural or spinal anesthesia, and their satisfaction with these procedures. Finally, the reason for admission, indication for LP, and suspected diagnosis as given by the treating ward physicians were noted.

#### Informed consent procedure (ICP)

2.12.2

The ICP was performed according to the group-specific protocol (see Supplementary Text S1). It was registered whether or not the patient requested a copy of the signed information printout, and the time spent with the patient for the ICP was noted. The informed consent discussion was audio-recorded using a small recorder in the physician’s lab coat; the recording began just before the physician entered the room and was terminated directly after she left the room. The audio recording was later transcribed to control for adherence to the protocols, and any patient-identifying contents were removed.

#### Survey time point 2 (t2)—directly after ICP

2.12.3

After completion of the ICP, the study physician informed the study assistant that the patient could now be approached for the t2 survey. Although there was no prespecified delay between the ICP and t2, the study physician waited for several minutes to ensure that the study assistant could not know the true duration of the ICP and was, therefore, not at risk of being unblinded. The survey at t2 only included questionnaires that the patients completed on the tablet by themselves. Five items from the Treatment Expectation Questionnaire were modified to fit the purposes of the study (modified TEX-Q) (Shedden-Mora et al., 2023). These items measured the extent to which patients regarded the procedure as being associated with expected: (1) burden, (2) undesirable effects, (3) pleasant course, (4) satisfaction with the procedure, and (5) personal responsibility for its success. The state subscale of the State–Trait Anxiety Inventory (STAI-state) includes 20 items and was used to assess state anxiety after ICP (Ferreira and Murray, 1983; Laux et al., 2013).

#### Lumbar puncture (LP)

2.12.4

The patient was approached in his/her hospital room for the LP. Once the patient had adopted the required position and the physician had thoroughly disinfected the skin area, prepared a sterile field, and was just putting on sterile gloves, the patient was asked to rate how nervous he/she currently felt about the imminent LP on an NRS from 0 (not at all) to 10 (worst imaginable nervousness). Upon successful puncture (indicated by CSF backflow), the patient was asked to rate the pain during needle insertion from 0 (no pain at all) to 10 (worst imaginable pain). After completion of the procedure, the physician left the room and immediately noted the number of necessary needle insertions into the skin until successful CSF drainage, the size and length of the needle used, and the total number of milliliters of CSF collected. The total contact time between physician and patient (from the physician entering to leaving the room) was noted.

#### Survey time point 3 (t3)—3 h after LP

2.12.5

Three hours after completion of the LP, the patient was asked to complete the next survey on the tablet. The survey asked about current pain in the needle insertion site (NRS 0–10), congruence with the patient’s expectation about the course of the procedure (yes, as expected/better than expected/worse than expected), and generic symptoms and their attribution to the LP using the modified GASE (nausea, headache, dizziness, back pain, visual disturbances, hearing disturbances, abnormal sensations, phono- or photophobia, or other complaints specified by the patient). Current headache intensity (NRS 0–10), headache-related impairment since LP, duration of headache (in minutes), and minimum, maximum, and mean headache intensity since LP were further assessed (NRS 0–10). If patients had requested a print copy of the ICP leaflet, they were asked to indicate whether they had read it (no/partially/entirely) and if so, whether they found it useful (yes/no). Warmth and competence of the physician were evaluated and general satisfaction with the procedure was rated (Seewald and Rief, 2023). To account for potential behavioral influences on headache after LP, the amount of fluid intake and the duration of bed rest since LP were noted. If patients reported headache, the interviewer structurally assessed headache history in more detail in terms of quality, localization, accompanying symptoms (features of migraine or trigeminal-autonomic headache), and exacerbating factors (physical activity, orthostatic features) to check whether the headache could be assigned to a specific headache disorder such as PDPH or migraine, as characterized by the International Classification of Headache Disorders (ICHD-3). Finally, the utilization and effectiveness of on-demand pain medication (against headache or other pain) since LP were assessed.

#### Survey time point 4 (t4)—24 h after LP

2.12.6

The patient was approached for t4 24 h after completion of the LP. As at t3, generic and specific side effects since the last survey (t3) were assessed using the modified GASE. Similarly, headache-related impairment since t3, and if applicable, duration, minimum, maximum, and mean headache were noted, and headache features were recorded. Again, utilization and effectiveness of on-demand pain medication were noted.

#### Survey time point 5 (t5)—72 h after LP

2.12.7

T5 took place 72 h after completion of the LP and contained the same questions as at t4, relating to the time since the last survey. Patients were also asked to guess the group they believed they had been assigned to (application of the current standard procedure vs. application of the new test protocol) through one additional question in the tablet-based survey.

#### Survey time point 6 (t6)—3 months after LP

2.12.8

A final online survey and telephone interview were conducted 3 months (target: 12 weeks = 84 days) after LP as a follow-up. The online survey assessed generic symptoms in the past 7 days and their attribution to the LP (modified GASE), the overall satisfaction with the LP, current headache intensity, headache-related impairment since LP, and minimum, maximum, and mean headache intensity. Participants’ beliefs about their study group allocation and the study’s overall goal were also queried. In the telephone interview, patients’ knowledge of their diagnosis and their illness perception were assessed again (modified B-IPQ). Finally, patients were asked whether they had a known diagnosis of primary headache and whether the number of days with headache and of days requiring pain medication due to headache per month had changed between the 3 months before and the 3 months after LP. Specifically, the occurrence of a new headache that persisted and never faded for at least 15 days since LP was queried. Headache characteristics were assessed again to determine their alignment with a specific headache disorder.

### Data management

2.13

In addition to the participant consent and the participant list, personal data are stored exclusively in pseudonymized form. Pseudonymized survey data collected using LimeSurvey is exported and stored on the University Medicine Essen Cloud, and a copy on an external hard drive is securely deposited and locked in the facilities of the Department for Clinical Neurosciences and Translational Pain Research at Essen University Hospital. The pseudonymized data will also be analyzed within the framework of the Collaborative Research Center SFB 289 on “treatment expectation” (see text footnote 1, central project lead by senior author [name]) provided that the patient has given separate consent for this.

The paper-based participant consent forms and sheets that contain the full names and contact details of the participants will be stored separately at the study site for 10 years and will not be transferred into electronic form. We are committed to sharing anonymized raw data alongside analysis codes from all results presented in future publications from this study.

### Analysis plan

2.14

Data will be analyzed in R (R Core Team).^2^

#### Main outcome: headache-related impairment

2.14.1

We hypothesize that headache-related impairment (main outcome) will be lower in the OPT group than in the SOC group during the main investigation period, assessed at three time points: 3 h (t3), 24 h (t4), and 72 h (t5) after LP. To test this hypothesis using a 2×3 mixed factorial study design, we will apply two-way repeated measures analysis of variance (ANOVA) to calculate an F-statistic on the main effect of the factor group (OPT vs. SOC) as well as the interaction effect between group and time point. The significance level (alpha level, type II error rate) for the probability over F (Pr(>F), *p*-value) will be set at 0.05. If *p* < 0.05, *post hoc* contrasts with correction for multiple comparisons (Bonferroni–Holm) will be performed. If the data do not meet assumptions of normality and homoscedasticity, we will instead use aligned rank transform ANOVA as the non-parametric alternative for the assessment of main effects and interactions (Wobbrock et al., 2011). The study will follow a per-protocol approach for the analysis.

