### Trial design

2.1

This prospective study was conducted using a parallel-group design with two groups. In the experimental group, the optimized communication protocol was applied (OPT), whereas the standard-of-care group (SOC) received communication according to a control protocol that uses standard communication observed in the clinic with no particular consideration of the effects of communication. The required sample size for the planned analysis of the main outcome (i.e., complete datasets from t1 to t5) was N = 80 inpatients, recruited in the general wards of the Neurology Department at the University Hospital Essen, with a balanced 1:1 group allocation ratio (n = 40 for SOC, n = 40 for OPT). The study was preregistered at the German Clinical Trials Register (DRKS00032272). This study protocol aligns with the SPIRIT guidelines (Standard Protocol Items: Recommendations for Interventional Trials) and follows the SPIRIT-PRO extension for patient-reported outcomes, as specified in Supplementary Table S1 (Chan et al., 2013; Calvert et al., 2018).

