### Sample size, randomization, and blinding

2.7

The sample size of N = 80 for the final analysis was chosen for reasons of feasibility while ensuring sufficient power to detect a clinically meaningful effect. With a power of 0.90, the study can detect an effect size f of at least 0.16 for the interaction effect between the group and time point on the primary outcome measure (headache-related impairment) (G*Power 3.1.9.7). This corresponds to a small to medium effect size. The recruitment period was set at 6 months (December 2023–May 2024), based on predetermined staff resources and estimates of the expected number of eligible study patients from recruitment from the wards. This timeline was expected to yield an effective sample size of 80 participants, accounting for an anticipated attrition rate of 15%.

Group allocation was performed after enrollment (i.e., after patients had provided written informed consent) via clustered block randomization, with a block consisting of 10 sequentially enrolled patients. To minimize the risk of communication between participants potentially influencing the outcomes, which can be a concern in settings like inpatient stays, the entire block was assigned to the same group. The sequence of all blocks was randomized before the start of the study based on a randomization list created in R. The last block of each group was truncated and ended as soon as the targeted sample size of n = 40 per group (not counting dropouts) was reached. The randomization list and the mode of randomization (clustered block randomization) were concealed from the blinded study assistant, who was responsible for recruiting and data collection, as well as from the clinical staff, to avoid unintended indirect influences from nurses or treating ward physicians. Only the study physician performing the ICP and LP according to the group allocation had the randomization list and was unblinded to group allocation.

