#### Exploratory analyses

2.14.3

The number needed to treat with optimized communication to prevent a certain level of headache-related impairment can be assessed exploratively (e.g., greater than 2 out of 10). Analyzing differences in reported side effects other than headache (assessed in the modified GASE questionnaire) allows us to test whether the optimized communication strategy influenced a wider range of side effect symptoms. Furthermore, the dataset lends itself to the exploration of associations between the study’s outcomes and demographic as well as baseline psychometric characteristics (e.g., age, sex, trait anxiety, trait depression), as their contribution to the outcomes can be controlled for and potential influences between outcomes, that is, through modulation, can be explored. The importance of perceived warmth and empathy of the physician—largely influenced by non-verbal communication—will be examined by analyzing the variance in side effect outcomes explained by patients’ ratings of the physician’s warmth, also probing for a potential modulatory influence on the group effect. The exploratory analyses are intended to make novel discoveries and help generate new hypotheses regarding biopsychosocial mechanisms through which the optimized communication might act or regarding predictive factors that might identify patients who benefit most from our optimized communication protocol.

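### The primary model leaves out baseline headache, which is recorded before the intervention; adjusting would sharpen the group comparison by an amount the documents do not let one fix

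*Protocol article*

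**What the plan says.** Section 2.14.1 (Main outcome) gives the primary method: "To test this hypothesis using a 2×3 mixed factorial study design, we will apply two-way repeated measures analysis of variance (ANOVA"). The tests named are the group main effect and the group-by-time interaction over t3, t4 and t5. If assumptions fail, an aligned rank transform ANOVA replaces it. No covariate is named in either.

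Section 2.12.1 (t1, baseline) describes two headache measures taken before the consent discussion. One is a current rating: "Current headache intensity was assessed on a numerical rating scale (NRS) from 0 to 10". The other is the headache item of the modified GASE, which covers the preceding seven days. Table 2 lists both at t1.

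Section 2.14.3 (Exploratory analyses) is the only place that mentions control for baseline characteristics: "as their contribution to the outcomes can be controlled for". Its examples are age, sex, trait anxiety and trait depression; headache is not among them.

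Section 2.4 (Exclusion criteria) removes patients with a chronic headache condition, with 15 or more headache days in the last 30, or with headache as the main reason for admission or puncture. Patients with fewer headache days and none of these features remain eligible.

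**The concern.** A patient who already has headaches may report headache impairment after the puncture whatever was said during consent. The impairment item is anchored in time (since the puncture or the last survey), but the score does not net out headache that would have occurred anyway. If t1 headache predicts the score, leaving it out has two costs. Its share of the between-patient variance stays in the error term of the group comparison. Any chance difference between arms in baseline headache also passes uncorrected into the estimate of the one trial that was run. With 40 patients per arm and no stratification described, both deserve attention, and the variables needed are already in the data set.

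**Working it through.** **Inputs from the protocol article**
- Analysed N: "The sample size of N = 80 for the final analysis was chosen for reasons of feasibility" (section 2.7). The figure is net of dropout ("accounting for an anticipated attrition rate of 15" per cent), so 80 is the right N here.
- Allocation: "with a balanced 1:1 group allocation ratio" (section 2.1), that is 40 per arm.
- Significance level: "will be set at 0.05" (section 2.14.1).
- Power statement: "With a power of 0.90, the study can detect an effect size f of at least 0.16 for the interaction effect" (section 2.7).
- Number of outcome measurements: m = 3.

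**Assumed, because the documents do not state them:** correlation between repeated measurements ρ = 0.5 and sphericity ε = 1; baseline–outcome correlation r = 0.1, 0.3, 0.5; block intraclass correlation (ICC) 0.05 and 0.10.

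**1. The plan's own figure.** For the interaction, λ = N·m·f²/(1 − ρ) = 80 × 3 × 0.0256/0.5 = 12.29 on 2 and 156 degrees of freedom. Power is 0.885, and the f detectable at exactly 0.90 is 0.164, which rounds to 0.16. The figure is reproduced.

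**2. Which test gains.** The group main effect compares patients' mean scores over t3 to t5. Let r be the within-arm correlation of t1 headache with that mean. The error variance of the group effect is then multiplied by 1 − r², and effective N = 80/(1 − r²). For this test λ = N·m·f²/[1 + (m − 1)ρ] = 120·f², divided by 1 − r² after adjustment, with one error degree of freedom lost.

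| Assumed r | 1 − r² | 80/(1 − r²) | Power if 80% unadjusted | f detectable at 90% power |
|---|---|---|---|---|
| unadjusted | 1 | 80 | 80.0% | 0.300 |
| 0.1 | 0.99 | 80.8 | 80.4% | 0.298 |
| 0.3 | 0.91 | 87.9 | 83.6% | 0.286 |
| 0.5 | 0.75 | 106.7 | 89.9% | 0.260 |

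**3. Which test does not gain.** A single covariate that is constant over time cancels from within-patient differences, so the interaction test in step 1 is essentially unchanged.

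**4. Chance imbalance.** Under individual randomisation, the SD of the baseline difference between arms is √(2/40) = 0.224 SD. P(|difference| ≥ 0.3 SD) = P(|Z| ≥ 0.3/0.224) = 0.18. With blocks of 10 the SD becomes √[(2/40)(1 + 9·ICC)]:
- ICC 0.05: 0.269 SD, probability 0.265.
- ICC 0.10: 0.308 SD, probability 0.33.

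An imbalance of 0.3 SD moves the unadjusted estimate by r × 0.3, that is 0.03, 0.09 or 0.15 outcome SD at r = 0.1, 0.3 or 0.5.

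**5. Clustering.** Simulation with 4 blocks of 10 per arm, ICC 0.05 in baseline and residual outcome, 6,000 runs. Type I error without and with the covariate was 0.1175 and 0.1133 at r = 0.3, and 0.1047 and 0.1075 at r = 0.5. Adjustment does not restore the nominal 0.05.

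**The case against.** The unadjusted comparison is a valid analysis, and nothing in section 2.14.1 is false. That stands: the point is about efficiency and the conditional accuracy of the estimate. It is still fair to raise, because the article states the model's terms and places covariate control among exploratory work.

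The size of the gain is unknown. This also stands. The exclusions in section 2.4 narrow the range of baseline headache, and the t1 items measure intensity and symptom severity, not impairment. A correlation near 0.1, with a negligible gain, is plausible. A covariate need only be prognostic, however, so the mismatch of items does not rule out adjustment.

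Three stronger readings are tempting, and the documents do not support them.
- A reader might infer that allocation by a handful of blocks makes the unadjusted result biased by baseline headache. Chance imbalance does not bias the estimate over repeated randomisation, and any excess over 18% rests on an ICC the documents do not give.
- A reader might infer that adjustment repairs the block design. Step 5 of the working shows that it does not; clustering is a separate issue.
- A reader might infer that the trial as powered gains up to a third in sample size (107 against 80). The power statement concerns the interaction, which gains essentially nothing.

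It could also be said that the study can separate old from new headache, since t3 to t5 record symptom attribution to the puncture and headache features. Those data exist, but they do not enter the primary score.

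Finally, enrolment was set to end in May 2024 and the trial is preregistered, so a change of primary model now would be late. This stands and shapes the fix.

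**Conclusion.** The point holds in a limited form. The primary model omits a baseline variable that is already collected, precedes the intervention and may well be prognostic. For the group main effect, which is the stated hypothesis, adjustment would give 80 patients the information of about 81, 88 or 107 at assumed r = 0.1, 0.3 or 0.5, and would remove the effect of any chance imbalance in baseline headache. The variance formula applies to the ANOVA; for the rank-based fallback it is only a guide. The benefit does not extend to the group-by-time interaction or to the clustering. This is a worthwhile improvement to a valid analysis, with a gain that runs from trivial to useful depending on an r nobody can read from the documents.

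**What to change.** - In section 2.14.1, add t1 headache (current intensity, the past-7-day GASE headache item, or both) as a prespecified covariate in the primary model. Do the same for the headache-intensity models in section 2.14.2.
- State a covariate-adjusted form of the fallback, so that adjustment does not disappear if assumptions fail. One option for the group effect is Quade's rank analysis of covariance on each patient's mean impairment.
- Report the unadjusted result beside the adjusted one.
- Date the change before any group comparison is seen. If comparisons have already been seen, keep the preregistered unadjusted model as primary and report the adjusted model as a labelled sensitivity analysis.

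The cost is one or two degrees of freedom and a documented change to the preregistered analysis. No new data are needed.
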